### Neuroventure: neuroimaging add-on study

#### Participants

Neuroventure will focus on high-risk students with SS and IMP personality profiles as they contribute most to the prediction of early onset substance-related behaviors in adolescence [42]. Thus, a subsample from the Co-Venture Trial of 60 high SS (30 of whom will receive the intervention), 60 high IMP (30 of whom will receive the intervention) and 30 low-risk (low SS and low IMP will not be invited to participate in the interventions) Grade 7 students (50% girls) will be invited to participate in this neuroimaging study (Please refer to Fig. 1 for the consort diagram and to Fig. 2 for the actual recruitment data). An independent informed consent from parents and adolescents will be obtained for the present study. Exclusion criteria will include major neuro-developmental disorders (e.g., autism), uncorrectable visual impairment or hearing deficits, severe mental health problems (e.g., schizophrenia, bipolar disorder), uninterruptable central nervous system medication, and any magnetic resonance imaging (MRI) contraindications (e.g., pregnancy, braces, etc.).

**Fig. 1 Fig1:**
[figure not shown]
Consort diagram for the Neuroventure Study. *For the Neuroventure project, we considered a low-risk personality to have a z-score below 0.5 on both Negative thinking (NT) and Anxiety sensitivity (AS) traits, and a z-score below 0.0 on both SS and IMP traits, to be adequate matches for the SS and IMP groups

**Fig. 2 Fig2:**
[figure not shown]
Recruitment data in the still ongoing project. *For the Neuroventure project, we considered a low-risk personality to have a z-score below 0.5 on both NT and AS traits, and a z-score below 0.0 on both SS and IMP traits, to be adequate matches for the SS and IMP groups. **A z-score above 1.0 on the SS personality trait. ***A z-score above 1.0 on the IMP personality trait

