## Methods

### Objectives and hypotheses

In 2011, the Co-Venture Trial was funded by the Canadian Institutes of Health Research (CIHR) to test the 4-year impact of the Preventure programme on delaying early onset drinking and binge drinking in students as well as long-term addiction outcomes. A subsequent CIHR grant was awarded for the Neuroventure study, allowing us to add longitudinal neuroimaging measures to test the following objectives/hypotheses:Compare high-risk (IMP and SS) and low-risk youth on measures of brain structure and function to quantify neurocognitive endophenotypes of these two risk profiles prior to exposure to alcohol in adolescence. We expect to observe impaired fronto-striatal connectivity and function during response inhibition in IMP as well as altered function of frontal and sub-cortical regions (i.e., basal ganglia and ventral striatum) during reward anticipation in SS.Measure the correlates of adolescent drinking and binge drinking on the development of brain structure and function in adolescence, controlling for baseline differences in personality, cognitive profiles, and neural measures that are implicated in the predisposition to early onset alcohol misuse. By comparing youth who take up drinking to those who do not (regardless of intervention status), we will test the extent to which binge drinking trajectories are associated with delayed or altered development of fronto-striatal and fronto-limbic networks that mediate response inhibition and anticipation of reward/punishment. Three hypotheses will be examined. i) Global effects: abnormalities will be observed systematically across all measures of brain function and structure, ii) Developmental specificity: alcohol-induced abnormalities will be specific to regions and cognitive processes that are maturing in adolescence, and iii) Interaction effect: alcohol will exacerbate the abnormalities shown to characterize each high-risk group at baseline.Test causal hypotheses by testing whether delaying drinking (through the Preventure Programme) can produce observable protective effects on structural and functional brain development. By comparing high-risk youth who received intervention to those who did not, we will estimate an intervention effect on structural and functional brain outcomes, which again might be expressed globally across the brain, or more specifically in those areas developing during adolescence or most abnormal in high-risk groups (as revealed in objective 1).

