
### The Co-Venture Trial (from which the participants are recruited)

This study uses a cluster-randomized controlled design in which 31 schools (cluster) agreed to conduct annual surveys for 5 years with all consenting adolescents (*N* = 3826) who were enrolled in Grade 7 in September 2012. Schools were randomly assigned to i) be trained and assisted in the delivery of the Preventure programme to Grade 7 high-risk adolescents or ii) not be exposed to the intervention. Adolescents were screened using the SURPS [36] during their Grade 7 year and invited to participate in personality-specific Preventure workshops if they scored one standard deviation above the school mean on one of the four SURPS dimensions. The Co-Venture clinical Trial is registered on www.ClinicalTrials.gov, “Co-Venture: a Cluster Randomized Trial Investigating the Effects of Selective Intervention on Adolescent Cognitive Development and Addiction”, study NCT01655615.

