#### Sample size justification

An estimated 125 subjects in total will be required to identify a moderate effect of personality group (high SS, high IMP, low-risk) on brain measures, prior to the initiation of alcohol use, with 4 covariates, critical F(2, 118) = 3.07, *p* = 0.05, 85% power. Another 25 participants will be added to the sample to allow for attrition (15% over 4 years, based on previous studies). This sample size will provide 90% power to assess moderate group differences in developmental trajectories of alcohol use (group by time interactions) within a longitudinal design with 3 repeated assessments and corrections for multiple testing, critical F(4240) = 3.40, *p* = 0.001. The current study will be sufficiently powered to detect two-year changes on functional and structural data, considering numerous previous studies of similar size showing moderate (*r* = .30) age-related activation in cortical and subcortical regions of the brain when performing fMRI tasks tapping attention and higher cognitive abilities [10]. Similar power is required to test the effects of intervention.

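### The SS and IMP groups are each defined on one trait with no limit on the other, so no single contrast among the three groups isolates one trait as Objective 1 requires

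*Protocol article*

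**What the plan says.** The Fig. 2 legend gives the only readable definitions of the two high-risk groups: "A z-score above 1.0 on the SS personality trait. *A z-score above 1.0 on the IMP personality trait". The same legend bounds the low-risk group on all four traits: "a z-score below 0.5 on both NT and AS traits, and a z-score below 0.0 on both SS and IMP traits". The parent trial's screening rule (The Co-Venture Trial) invites students "if they scored one standard deviation above the school mean on one of the four SURPS dimensions" and says nothing about a student above the threshold on two.

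The rest of the article treats SS and IMP as distinct groups. Participants plans "60 high SS (30 of whom will receive the intervention), 60 high IMP (30 of whom will receive the intervention", plus 30 low-risk youths. Sample size justification powers a "moderate effect of personality group (high SS, high IMP, low-risk) on brain measures". Objective 1 is to "quantify neurocognitive endophenotypes of these two risk profiles prior to exposure to alcohol in adolescence", with a different prediction for each profile: response inhibition for IMP, reward anticipation for SS. The covariates named under Statistical analyses are age, socioeconomic status, pubertal stage, IQ and other drug use, given as examples. Neither trait score is among them. Objective 2 mentions control for baseline personality; Objective 1 does not.

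**The concern.** A youth with SS = 1.2 and IMP = 1.6 satisfies both definitions. Wherever that youth is placed, the group receives someone high on the other trait too. Two things follow for Objective 1.

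First, the SS and IMP groups lie closer together on each trait than their labels suggest, which weakens the contrast meant to separate the two profiles. Second, the low-risk group is low on both traits, so a comparison of SS with low-risk youth is also a comparison of higher with lower IMP. A difference in reward anticipation found there cannot be credited to SS on that contrast alone, nor an inhibition difference to IMP on the mirror contrast. The SS-minus-IMP contrast does not settle it either: it estimates a difference between the two trait effects, which is near zero if both traits matter equally.

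**Working it through.** **The plan's own figure.** For a three-group ANCOVA with 4 covariates and N = 125, the error df are 125 − 3 − 4 = 118, and the 5% critical value of F(2, 118) is 3.073, as stated. With noncentrality N·f² and f = 0.30, power is 85.1%, also as stated. (The article says only that the effect is moderate; at f = 0.25 power would be 69.5%. That is a separate matter.) So there is no arithmetic error behind this point. The issue is what the three groups represent.

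**Inputs.** From the documents: the cut-off of 1.0 for each high-risk group, the low-risk limit of 0 on SS and IMP, and 60 youths per high-risk group. Assumed: standard bivariate normal z-scores with SS–IMP correlation r of 0 to 0.4. The low-risk limits on NT and AS are ignored, as if those traits were unrelated to SS and IMP.

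**Share high on both traits.** Let p = 1 − Φ(1) = 0.1587 and q = P(SS > 1 and IMP > 1).
- Each group mirrors its whole pool: share = q/p.
- Each dual-high youth goes to the group of the higher score: half of q goes to each side, so share = (q/2)/(p − q/2).

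At r = 0, q = 0.0252. This gives 0.0252/0.1587 = 15.9% and 0.0126/(0.1587 − 0.0126) = 8.6%.

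**SS-score separation between the SS and IMP groups.** The mean SS score given SS > 1 is φ(1)/p = 0.2420/0.1587 = 1.525. Given IMP > 1 it is 1.525·r. The whole-pool separation is therefore 1.525(1 − r). The higher-score and single-trait values come from simulating 6 million pairs. At r = 0 the single-trait value can be checked by hand: 1.525 + 0.2420/0.8413 = 1.525 + 0.288 = 1.813.

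| r (assumed) | q | Dual-high, whole pool | Dual-high, higher score | SS gap, single-trait | SS gap, higher score (loss) | SS gap, whole pool (loss) |
|---|---|---|---|---|---|---|
| 0 | 0.0252 | 16% (9.5 of 60) | 9% (5.2 of 60) | 1.813 | 1.698 (6%) | 1.525 (16%) |
| 0.2 | 0.0381 | 24% (14.4) | 14% (8.1) | 1.605 | 1.454 (9%) | 1.220 (24%) |
| 0.3 | 0.0455 | 29% (17.2) | 17% (10.0) | 1.498 | 1.333 (11%) | 1.068 (29%) |
| 0.4 | 0.0536 | 34% (20.3) | 20% (12.2) | 1.381 | 1.202 (13%) | 0.915 (34%) |

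Loss is 1 − (gap / single-trait gap). At r = −0.2 the whole-pool share is still 9%.

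**IMP difference carried by the SS versus low-risk contrast** (same simulation, higher-score assignment):

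| r | Mean IMP, SS group | Mean IMP, low-risk | IMP gap | SS gap | IMP gap / SS gap |
|---|---|---|---|---|---|
| 0 | −0.15 | −0.80 | 0.65 | 2.35 | 28% |
| 0.2 | 0.10 | −0.85 | 0.95 | 2.40 | 39% |
| 0.3 | 0.22 | −0.87 | 1.09 | 2.43 | 45% |
| 0.4 | 0.36 | −0.89 | 1.24 | 2.44 | 51% |

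By symmetry the IMP group's own-trait gap equals the SS gap shown. So if a brain measure depended linearly on IMP alone, the SS versus low-risk contrast would still show 28–51% of the difference seen for IMP versus low-risk.

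**Removing dual-high youths does not cure this.** At r = 0, single-trait SS youths have mean IMP −0.288 and low-risk youths −0.798, a gap of 0.51 SD. At r = 0.4 the simulated gap is 0.98 SD. A tie-break or an exclusion helps the SS-versus-IMP comparison; only adjustment for the other trait addresses the comparison with low-risk youth.

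**The case against.** The article condenses a fuller protocol, and Figs. 1 and 2, to which Participants refers the reader, are not shown. The legend states a threshold and does not claim to be the whole allocation rule, so a tie-break may well exist. This stands: the absence of a rule is not shown, and the higher-score columns above are what one would see if that rule is in use. It answers only part of the point, because a tie-break leaves dual-high youths in each group and leaves the IMP gap to the low-risk group.

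Group analysis is also a legitimate choice for a sample recruited as groups, and the power statement rests on it. This stands too, and is a reason to keep the three-group comparison rather than replace it.

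A reader might infer more than the documents support:
- *That youths are counted twice.* The totals of 60 + 60 + 30, and of 120 high-risk plus 30 low-risk youths in the Abstract, point to single placement.
- *That 16–34% is the expected overlap and loss.* Those figures describe groups drawn to mirror their whole pools, the less favourable of the two scenarios.
- *That the intervention effect is blurred in the same way, or that imaging group and workshop trait disagree.* Objective 3 compares high-risk youth with and without the intervention, and no trait-specific intervention contrast is stated. Workshop allocation belongs to the parent trial, whose procedures are not shown. The pooled intervention contrast is little affected.
- *That a known share of each group has NT or AS as its highest trait.* This would need correlations that the documents do not give.

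**Conclusion.** The point holds in a limited form. As written, the SS and IMP definitions are not mutually exclusive, and the low-risk group is low on both traits. No single contrast in the three-group ANCOVA therefore isolates one trait, although the hypotheses of Objective 1 are trait-specific. For r from 0 to 0.4, about 9–20% of each group is high on both traits under higher-score assignment, with 6–13% of the SS-score separation lost. If each group mirrors its pool, both figures are 16–34%. The SS versus low-risk contrast carries an IMP difference of about 0.65–1.24 SD under higher-score assignment.

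The sizes rest on bivariate normality and an assumed correlation. The direction does not depend on the exact value chosen, since some overlap remains even at r = −0.2. The stated power for the three-group test and the pooled high- versus low-risk comparison are not called into question here.

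**What to change.** 1. Keep the three-group comparison as powered in Sample size justification.
2. For the trait-specific hypotheses of Objective 1, add a model with the continuous SS and IMP screening z-scores entered together, low-risk youth included, so that each trait's effect is adjusted for the other.
3. State how youths above 1.0 on both traits are assigned to an imaging group (for example, by the higher z-score) and report how many there are.
4. Repeat the SS-versus-IMP comparison without those youths as a sensitivity analysis.

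The cost is small, because the SURPS scores already exist and no recruitment or new data are needed. There are three downsides: one more model to report, a linearity assumption across a middle range that the cut-offs leave sparsely sampled, and a smaller sample in the sensitivity analysis.

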#### Procedure

Eligible students will be invited to attend three identical scanning sessions over a 5-year period: the first session during the baseline year of the Co-Venture Trial (for intervention schools, this would refer to the period prior to when intervention sessions are run), and second and third session 24 and 48 months later, respectively (Grade 9 and 11). Participants will undergo a 65-min structural and functional neuroimaging assessment, and will complete a 2-h battery of neuropsychological tasks post-scan. In addition, participants will be assessed on substance use, global IQ and behavioral measures annually for 4 years post intervention through the Co-Venture Trial.

#### Behavioral assessment

Adolescents will be administered the Timeline Follow-Back Interview [43, 44] to assess past 6 months alcohol and drug use in a face-to-face interview.

To evaluate cognitive functioning, adolescents will complete the STROOP [45], a measure of response inhibition. To evaluate non-spatial and spatial working memory, participants will be administered the Self-Ordered Pointing Test (SOPT; [46]), and the N-back task [47] (the 2- and 3-Back versions). The Children’s memory scale (CMS)-Dot Location [48], a sub-test of the CMS, will be used to assess spatial immediate and deferred memory recall. The participants will also complete the computerized Balloon Analogue Risk Task (BART: [49]). The BART assesses real-world risk taking behavior by balancing the potential for reward (inflating the balloon) versus loss (balloon exploded). Finally the sub-tests of the Vocabulary and Block Design will be used as an estimate of the Wechsler Intelligence Scale for Children 4th Edition [50] full scale IQ.

#### Scanning protocol

Functional MRI (fMRI) data will be acquired on a 3T Siemens Magnetom Trio MRI scanner using whole brain gradient echo planar imaging (EPI) sequence sensitive to blood oxygenation level dependent (BOLD) contrast in 47 slices (Repetition time (TR) = 2.5 s; Echo time (TE) = 30 ms; 3 mm thickness; voxel size: 3 × 3 × 3 mm^3^). A higher resolution structural scan using an ultrafast gradient echo 3D sequence (MPRAGE) will also be collected for structural analyses and to aid functional data registration (TR = 2.3 s; TE = 2.96 ms; 1 mm thickness; voxel size: 1 × 1 × 1 mm^3^). Diffusion weighted imaging (DWI) data will be acquired during a peripherally gated spin echo EPI sequence with diffusion sensitization gradients (‘b value’ of 100 s/mm^-2^) applied in 64 directions (HARDI protocol); this will provide whole brain coverage at 2.0 mm isotropic resolution.

Rapid, event related, BOLD fMRI will be performed while participants complete tasks that engage two specific domains of cognitive performance: a modified version of the Monetary Incentive Delay Task (MIDT) and a motor response inhibition task (Stop-Signal task) (for further details please refer to [51]). The MIDT has been used extensively to investigate changes in neural activity in response to different stages of reward processing (e.g., anticipation, outcome processing, and consumption), as well as the processing of tasks under different reward conditions [52]. This modified version uses non-monetary incentives (points) to invoke anticipation of reward and punishment. Participants’ outcome (score) is dependent upon their performance in a simple reaction time task, divided into control (no reward or punishment – 32 trials), potential reward (win 10 points – 32 trials) and potential punishment (lose 10 points – 32 trials) sub-tasks. The MIDT is sensitive to developmental and individual differences in sensitivity to cues for reward and punishment and three studies show relationships between ventral striatal activation on this task and risk taking and/or substance use in the IMAGEN sample [53–55]. The fMRI adaptation [56–59] of the Stop-Signal Task [60] measures activity in brain areas related to the inhibition of an already planned motor response as well as error detection. On a total of 300 trials, a motor response to high frequency go signals (75% of trials) has to be inhibited when infrequently and unexpectedly (in randomized 25% of trials), a stop signal appears after the go signal. The task is individually titrated to force every subject to fail on 50% of stop trials, making every subject work at the edge of their own inhibitory capacity, and therefore adjusting for differences in success levels between subjects and groups, making it ideal for developmental studies [56, 58, 59]. The fronto-striato-thalamic network during successful inhibition shows a progressive functional maturation between childhood and adulthood [56].

#### Sample size justification

An estimated 125 subjects in total will be required to identify a moderate effect of personality group (high SS, high IMP, low-risk) on brain measures, prior to the initiation of alcohol use, with 4 covariates, critical F(2, 118) = 3.07, *p* = 0.05, 85% power. Another 25 participants will be added to the sample to allow for attrition (15% over 4 years, based on previous studies). This sample size will provide 90% power to assess moderate group differences in developmental trajectories of alcohol use (group by time interactions) within a longitudinal design with 3 repeated assessments and corrections for multiple testing, critical F(4240) = 3.40, *p* = 0.001. The current study will be sufficiently powered to detect two-year changes on functional and structural data, considering numerous previous studies of similar size showing moderate (*r* = .30) age-related activation in cortical and subcortical regions of the brain when performing fMRI tasks tapping attention and higher cognitive abilities [10]. Similar power is required to test the effects of intervention.

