Functional image analysis will be carried out using FSL (FEAT – FMRI Expert Analysis Tool). The following pre-processing steps will be applied: motion correction using MCFLIRT [68], non-brain removal using BET [69], and spatial smoothing with a Gaussian kernel of FWHM 6 mm. Time-series general linear model will be carried out using FILM with an autocorrelation correction [70]. At the first level, the following contrasts: anticipation/feedback of win and lose *vs* reference (MIDT) and successful and failed inhibition *vs* baseline (Stop-Signal Task) will be estimated for each participant. Group-level (second level) analysis will be carried out using a fixed effects model, by forcing the random effects variance to zero in FLAME (FMRIB’s Local Analysis of Mixed Effects) [71]. *Z* (Gaussianised T/F) statistic images will be thresholded using clusters determined by *Z* > 2.3 and a corrected cluster significance threshold of *p* = 0.05.

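### In the longitudinal power statement the degrees of freedom, critical F and significance level do not fit together: F(4,240) = 3.40 is the 1% point, not the 0.1% point

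*Protocol article*

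**What the plan says.** The protocol article, under Sample size justification, contains two calculations. The first sets the required number at 125, for a comparison of three personality groups on brain measures with four covariates: critical F(2,118) = 3.07 at p = 0.05 with 85% power. Another 25 participants are added for attrition.

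The second calculation is the one at issue. It states: "This sample size will provide 90% power to assess moderate group differences in developmental trajectories of alcohol use". The test is a group-by-time interaction, placed "within a longitudinal design with 3 repeated assessments and corrections for multiple testing". The threshold is given as "critical F(4240) = 3.40, *p* = 0.001". The effect is called moderate, but no numeric effect size and no correlation between assessments is given. No other section states a different level for this test.

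**The concern.** A critical value is fixed by its degrees of freedom and its significance level, so the three figures can be checked against each other without any assumption about the trial. Here they disagree, and the gap is a factor of ten in the level. The 90% power is attached to this threshold, and the sentence presents the threshold as already allowing for multiple testing. As printed, a reader would credit the study with 90% power at a level of 0.001, a combination that the printed cut-off does not deliver.

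**Working it through.** **Inputs** (protocol article, Sample size justification): three groups, "personality group (high SS, high IMP, low-risk"; 3 assessments; cut-off 3.40; level 0.001; power 90%; 125 required and 150 recruited.

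**Step 1: the degrees of freedom.** The printed 4240 is read as 4 and 240 with a lost comma. Three groups and three assessments give a numerator of (3 − 1) × (3 − 1) = 4. The denominator is (N − 3) × (3 − 1) = 240, which gives N = 123, close to the stated 125.

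**Step 2: check the convention on the other figure.** The upper 5% point of F(2,118) is 3.073, which matches the printed 3.07. The section therefore uses ordinary upper-tail F quantiles.

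**Step 3: test the printed triple.** For F(4,240):

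| Upper-tail level | Critical value |
|---|---|
| 0.05 | 2.409 |
| 0.01 | 3.398 |
| 0.001 | 4.778 |

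P(F(4,240) > 3.40) = 0.00997. The printed cut-off is the 1% point rounded to two decimals. The stated level of 0.001 is not reproduced.

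**Step 4: try other readings.**
- Degrees of freedom (4, 4240), taking the digits as a lost 4: 3.32 at 1% and 4.63 at 0.1%. Neither is 3.40.
- Three groups, three assessments and N from 123 to 150: the 0.1% point lies between 4.75 and 4.78.
- Five cells (SS and IMP, each with and without intervention, plus low-risk), three assessments and N = 125: numerator (5 − 1) × 2 = 8, denominator (125 − 5) × 2 = 240. The 0.1% point of F(8,240) is 3.4055, and P(F(8,240) > 3.40) = 0.00102. This is close, but it rounds to 3.41 and contradicts the printed numerator of 4.

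**Step 5: what the mismatch means for power, on the printed figures.** Take the noncentral F with 4 and 240 degrees of freedom and solve P(F > 3.40) = 0.90 for the noncentrality. The answer is 21.33. With that noncentrality, P(F > 4.778) = 0.718. If 90% was rounded from 89.5% or 90.5%, the result is 70.8% or 72.7%. Keeping 90% at 0.001 needs a noncentrality of 28.77, and 28.77 / 21.33 = 1.35, about 35% more.

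**Step 6: how far the power depends on what is not stated.** Assume noncentrality = f² × N × 3 / (1 − ρ) with N = 123, where f is the effect size and ρ the correlation between assessments (both my assumptions):

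| f | ρ | Noncentrality | Power at 0.001 |
|---|---|---|---|
| 0.20 | 0 | 0.04 × 369 = 14.8 | 44% |
| 0.20 | 0.3 | 14.76 / 0.7 = 21.1 | 71% |
| 0.25 | 0 | 0.0625 × 369 = 23.1 | 77% |
| 0.25 | 0.3 | 23.06 / 0.7 = 32.9 | 95% |
| 0.25 | 0.5 | 23.06 / 0.5 = 46.1 | over 99% |

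The row with f = 0.20 and ρ = 0.3 gives 90% at the 0.01 level, which agrees with the printed cut-off. The true power at 0.001 cannot be recovered from the article alone.

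**The case against.** The strongest reply is that this may be a misprint with no loss of power. If 0.001 should read 0.01, the cut-off and the 90% agree and only the level changes. If the calculation used the five cells of the design, N = 125 gives exactly 240 denominator degrees of freedom and a 0.1% point within 0.01 of 3.40. The level and the 90% could then both stand, with only the numerator misprinted. The section names 125 and nowhere mentions 123, which lends this reading some weight. With f = 0.25 and ρ = 0.3 (assumed), the power on that reading is 88%.

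This stands as a reason not to announce which figure is wrong. It does not rescue the sentence, because every reading leaves at least one printed figure to correct.

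Two further replies also stand. The number recruited does not depend on this sentence, since the 125 comes from the first calculation, which reproduces. And the sentence concerns "moderate group differences in developmental trajectories of alcohol use" between groups. A reader might infer that Objectives 2 and 3 are therefore underpowered, but the documents do not support that. Objective 2 compares youth who take up drinking with those who do not, and Objective 3 compares intervention with no intervention. Each is a two-group contrast with a different numerator, and the article treats intervention power in a separate sentence.

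**Conclusion.** The inconsistency is certain: with 4 and 240 degrees of freedom, 3.40 belongs to p = 0.01, and p = 0.001 requires 4.78. The power consequence is conditional. It is about 72% in place of 90% if the 90% was computed at the printed cut-off and 0.001 is the intended level. A reader might take 72% as the study's actual power. The article does not support that, because it gives neither effect size nor correlation and the misprint may lie elsewhere.

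A reader might also set this level against the fMRI analysis, which uses "a corrected cluster significance threshold of" 0.05, and infer an uncontrolled error rate across contrasts. That does not follow. The cluster threshold is already corrected within each map, nothing says the level of an alcohol-use test should govern imaging maps, and rules for multiplicity across contrasts may sit in an analysis plan that is not shown.

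This is a misstated threshold in one sentence. It should be corrected because the claimed power rests on it.

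**What to change.** Retrieve the original power calculation and restate the sentence in whichever form it supports:

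- (a) F(4,240) = 3.40, p = 0.01, 90% power; or
- (b) F(4,240) = 4.78, p = 0.001, with power recomputed (about 72% on the printed figures); or
- (c) if five cells were used, F(8,240) with a critical value of about 3.41 at p = 0.001, and the power confirmed.

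In each case give the numeric effect size and the within-subject correlation, so that the power can be reproduced. The change is one sentence and needs no extra participants. The price is that under (a) the stated level is less strict, and under (b) the stated power is probably lower.
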